### Effectiveness Evaluation

The evaluation protocol has been developed in order to address the objectives of the study through the following primary and secondary questions, formulated according to a PICO (population, intervention, comparator, outcome) framework [26]. It should be observed that, for feasibility purposes (due to educational block organizations in Swedish schools where many children change school between sixth and seventh grade), in this evaluation, the start of the intervention was set in the seventh grade (12- to 13-year old adolescents).

### Study Design

The evaluation questions will be addressed through a mixed-design approach, where experimental and nonexperimental designs will be combined.

#### Experimental Design

A parallel cluster randomized controlled experiment will be conducted with schools as units of randomization and individual students as unit of analysis. A superiority approach will be employed for hypothesis testing (ie, the null hypothesis to be rejected will be that the Tobacco-free Duo comprehensive intervention is either inferior or equivalent to the education-only component). Through this design, questions 1 to 5 will be addressed (Tables 1 and 2). The trial was registered (ISRCTN 52858080) on January 4, 2019 (ie, after enrollment of the first participant but prior to baseline assessments being completed).

**Table 1 table1:** Evaluation questions.

Objective–question		Formal question definition	

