The Swedish program *Tobacco-free Duo* is an example of this category of programs, addressing all forms of tobacco use. Details on the intervention and on its preliminary evaluation have been published [22-24]; however, firm conclusions on favorable effects of the intervention could not be reached due to weak study design or to methodologic shortcomings in these earlier evaluations. The Public Health Agency of Sweden commissioned this evaluation in order to strengthen the evidence base to be incorporated in possible future recommendations.

This commission was translated into the following specific objectives: (1) to assess whether the comprehensive Tobacco-free Duo program is superior to an education-only program in preventing onset of use of cigarettes or other tobacco among adolescents or in fostering smoking cessation among smoking parents, (2) to assess whether the adolescents or parents exposed to the core component of the program (adult-child agreement) refrained from using tobacco to a higher extent than those who were only exposed to other components of the program, (3) to explore the impact of the program on the whole school tobacco use prevalence over time, (4) to understand whether receipt of the program entailed negative side effects on the participating adolescents, and (5) to analyze school-level factors related to fidelity of the program implementation.

A health economic evaluation (cost-effectiveness study) will be conducted alongside the randomized controlled trial, and its corresponding protocol will be the object of a separate publication.

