**Objective 2**			
	Question 5		Is the probability of having refrained from using cigarettes or any tobacco by the end of follow-up higher among adolescents and parents who smoke who signed the formal agreement to become a tobacco-free pair (core component) compared to those who only received other components?
	Question 6		Is the proportion of sustained quitters (no smoking in the past 30 days) among parents who smoke before the program’s start higher when the index child attended a Tobacco-free Duo school compared to an education-only school, at the end of the compulsory grades?

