#### Nonexperimental (Observational) Design

Two different comparisons will be established. In the first comparison (addressing objective 2 question 6) an as-treated analysis of the trial data will be conducted where individual students assigned to the Tobacco-free Duo intervention and signing a child-adult contract will be contrasted to students receiving other Tobacco-free Duo components but not signing the contract. In the second comparison (addressing objective 3 question 7), all students attending schools in grades 7 to 9 in both experimental groups will be contrasted to students in a convenience sample of schools in the same broad catchment areas where the experiment takes place (an external reference group). Schools in this external reference group will be those willing to participate in the survey data collection but not in the experimental study. Therefore, they will represent the subset of schools in the target areas that will probably not be willing to adopt the program once released for dissemination. In Table 2, a summary is presented of the relevant comparisons established with an observational design.

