#### Data Analysis

Data from the trial will be analyzed primarily according to an intention-to-treat approach, preserving the random assignment [28]. Missing outcome information because of attrition at follow-up will be addressed by means of sensitivity analyses including last observation carried forward; best- and worst-case scenario, assuming missing answers as representing either the best or the worst outcome; and multiple imputation if a missing at random assumption for the missing data will not be dismissed [29].

Secondary analyses will be conducted per protocol, thus including only students in schools that adhered to at least 80% of the whole assigned intervention. Furthermore, an as-treated analysis will be conducted, comparing the outcome among students exposed to different components and intensities of the intervention, in particular the adoption of the core component *child-adult agreement* (research question 6). These approaches disregard randomization, therefore they are prone to producing biased estimates of the effect unless adjusted for most of the potential confounders [30]. However, they may be useful in order to assess the consistency between an expected effect and the intervention’s theoretical rationale [30] and in order to gain insights on the reasons for not detecting the estimated effect [31].

Finally, we will be able to compare the prevalence trends across 3 school years as well as the final prevalence at the end of follow-up between schools participating in the experimental study and schools in the external reference group, carrying on usual health education. This will enable us to estimate the potential impact of the intervention when released.

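### Questions 5 and 6 are numbered oppositely in Table 1 and in the text, and Table 2 defines the randomised parental-cessation comparison as contract versus no contract

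*Protocol article*

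**What the plan says.** Table 1 lists eight evaluation questions. Under Objective 2, Question 5 compares adolescents and smoking parents "who signed the formal agreement to become a tobacco-free pair (core component) compared to those who only received other components". Question 6, under the same objective, asks whether the proportion of sustained quitters among smoking parents is "higher when the index child attended a Tobacco-free Duo school compared to an education-only school, at the end of the compulsory grades".

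The Experimental Design section describes the cluster randomised superiority trial, in which "the null hypothesis to be rejected will be that the Tobacco-free Duo comprehensive intervention is either inferior or equivalent to the education-only component". It then says: "Through this design, questions 1 to 5 will be addressed (Tables 1 and 2").

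The Nonexperimental (Observational) Design section takes up the contract: "In the first comparison (addressing objective 2 question 6) an as-treated analysis of the trial data will be conducted". It describes that comparison as signers against non-signers among students assigned to Tobacco-free Duo. The Data Analysis section gives the same as-treated contract analysis the same number and comments on it at once: "research question 6). These approaches disregard randomization".

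On objectives, the Introduction defines Objective 1 as superiority of the full program over education only in preventing adolescent onset "or in fostering smoking cessation among smoking parents". The Abstract's objective (1) says the same.

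**The concern.** The link from question to design decides which results may be reported as randomised evidence. Question 5 of Table 1 compares people who chose to sign with people who did not. Question 6 compares parents by the arm to which their child's school was assigned. The first is open to confounding by whatever makes a family sign; the second is protected by randomisation.

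Read by number, the text places the first in the superiority trial and the second in an analysis that the protocol itself calls prone to bias. If the error were only one of digits, a careful reader could repair it. So the check is whether the remaining wording and Table 2 settle the intended analysis of each question. What is at stake is the one randomised comparison of smoking cessation in parents.

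**Working it through.** No figure is involved; this is a check of one place against another.

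**Step 1. The numbers.**

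| Place | Question 5 | Question 6 |
|---|---|---|
| Table 1, Objective 2 | Contract signers v non-signers | Parental cessation by school arm |
| Experimental Design | In the randomised design (1 to 5) | Left out of the randomised design |
| Nonexperimental Design | Not mentioned | As-treated contract comparison |
| Data Analysis | Not mentioned | As-treated contract comparison |

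The three places in the text agree with each other if 5 means parents by arm and 6 means the contract. Table 1 has the opposite. The objective label does not help, because Table 1 puts both questions under Objective 2.

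**Step 2. Can the digits be reconciled?** Yes, in two ways. Exchanging 5 and 6 in Table 1 makes all three places in the text consistent. Keeping Table 1 works if the Experimental Design section reads questions 1 to 4 and 6, and the other two sections read question 5.

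**Step 3. Adolescents.** Apart from the digits, the superiority null is stated by arm, which a comparison of signers with non-signers cannot test. Table 2 lists the adolescent contract contrast as nonexperimental and marks it as treated. The Nonexperimental Design section describes it in words, Data Analysis warns of bias, and the Discussion repeats that these groups are no longer randomised. The intended status is clear.

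**Step 4. Parents.** Table 2 has two parent rows:

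| | Experimental parent row | Nonexperimental row, Population 2 |
|---|---|---|
| Row title | Full program v education only, parental cessation | Effect of adhering to the contract |
| Population | Parents of trial adolescents, smokers at baseline | Parents of adolescents in the longitudinal assessment, smokers at baseline |
| Intervention | Signing a contract | Signing a contract |
| Comparator | Other components, no contract | Other components, no contract |
| Outcome | No smoking in past 30 days | No smoking in past 30 days |

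The contrast is identical in both. Only the title of the first row says that it is a comparison by arm.

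**Step 5. Why the contrast matters.** The contract belongs to the full program; education-only schools receive component 6 alone. Signing against not signing therefore either splits the Tobacco-free Duo arm, or sets its signers against a mixture of its non-signers and education-only parents. Neither preserves the random assignment. A signing adult also agrees to be tobacco free for the contract period, so smoking parents who sign are likely to be those already ready to stop.

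**The case against.** The strongest defence is that this is a slip in cross-references and that words outrank digits. For adolescents that defence stands in full, for the reasons in Step 3.

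It also has some force for parents. The as-treated comparison in the Nonexperimental Design section is described for students and does not mention parental cessation. Table 2 places a parental superiority row under its experimental heading, with a title by arm. Table 1's wording of the parental question is by school. All of this suggests that a comparison by arm was intended.

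The defence fails at the body of that row. The Experimental Design section sends the reader to Tables 1 and 2 for what the trial will test, and there the intervention and comparator are contract and no contract. Title and contents conflict, and correcting the question numbers leaves that conflict in place. A statistical analysis plan that is not shown might define the analysis correctly, but the contradiction within this document would remain.

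**Conclusion.** The point holds in a limited form. Two of the eight questions carry the wrong number in three places of the text relative to Table 1, and parental cessation by arm is filed under the wrong objective. For the adolescent contract question the error stops there. For parents, the experimental row of Table 2 also defines a self-selected contrast under a title that promises a randomised one, so the document does not fix which result will be reported as parental superiority.

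A reader might infer that two questions have been given the wrong design, or that the adolescent contract contrast will be presented as randomised evidence of superiority. The documents do not support that: they repeatedly describe it as as-treated and open to confounding. Nor can the numbering error be sized as a bias in the risk ratio. The document gives no signing rate and no data on what separates signers from non-signers, and any confounding in an as-treated analysis would be the same with perfect numbering.

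The primary outcome (Question 1), Questions 2 to 4, the target risk ratio of 1.10 and the sample of 3000 students are unaffected. The conclusion rests on reading the current text as printed and on no numerical assumption. It should be corrected before the parental results are analysed.

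**What to change.** 1. In Table 1, make parental cessation by assigned school Question 5 and move it to Objective 1; make the contract question Question 6 under Objective 2. The question numbers in the text are then right. Alternatively, keep Table 1's numbers, change the Experimental Design section to questions 1 to 4 and 6, and change the Nonexperimental Design and Data Analysis sections to question 5. The parental question still has to move to Objective 1 in that case.
2. In the experimental parent row of Table 2, restate intervention and comparator as Tobacco-free Duo schools against education-only schools, by random assignment. Leave the contract contrast in the nonexperimental Population 2 row only.
3. Add one sentence saying that the contract contrast, for adolescents and for parents, is not part of the superiority test.

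The cost is a few wording edits. No new data, sample size change or extra analysis is needed.

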**Objective 1**			
	Questions 1 and 3		Is the probability of having never smoked (question 1) or used any tobacco product^a^ (question 3) at the end of follow-up in the ninth grade higher for seventh-grade adolescents in schools assigned to the full program (Tobacco-free Duo components 1-6) compared to that of adolescents in schools assigned to conduct only the educational component (component 6)?
	Questions 2 and 4		Is the probability of never having progressed to regular (weekly during at least 3 consecutive months) use (question 2: smoking cigarettes; question 4: any tobacco product) by grade 9 higher for adolescents in Tobacco-free Duo schools than for those in education-only schools?
**Objective 2**			
	Question 5		Is the probability of having refrained from using cigarettes or any tobacco by the end of follow-up higher among adolescents and parents who smoke who signed the formal agreement to become a tobacco-free pair (core component) compared to those who only received other components?
	Question 6		Is the proportion of sustained quitters (no smoking in the past 30 days) among parents who smoke before the program’s start higher when the index child attended a Tobacco-free Duo school compared to an education-only school, at the end of the compulsory grades?
**Objective 3**			
	Question 7		Is the total prevalence of never smokers among students in the grades 7 to 9 declining more slowly over 3 years in Tobacco-free Duo schools compared to education-only schools or schools delivering their usual antismoking programs (external reference group schools)?

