#### Components

In brief, the program aims to mobilize antitobacco practices and attitudes in adolescents’ near environments, with schools as main promoters and arenas for the activities. The recommended starting point is in the sixth or seventh grade of compulsory school (between 12 and 13 years of age), and it encompasses 6 central components that were manualized in this study.

The tobacco-free pair (Duo) core component that is the origin of the program’s name consists of an agreement between an adolescent and a significant adult (at least 18 years old) elected as partner by the adolescents. The pair agrees to remain tobacco free during the following 3 years, at least, until the index adolescent leaves the compulsory school (about 15 years of age). The written agreement is signed by both partners, possibly during a public event in school, strengthening the mutual commitment. However, a pair can be formed anytime during the school year.Student information is given by a member of the school staff who informs the student in the sixth or seventh grade about the school choice to adopt the program, briefly discusses tobacco control issues, and actively encourages participation of the adolescents.Parent information is given during an ordinary parent meeting at school where they are given access to information and materials explaining their role in tobacco prevention and how they can actively support their children in their commitment.As an incentive to participate, all adolescents signing a contract will receive a membership card that entitles them to some fringe benefits in local shops or leisure-time activities.At the end of each school year, the pairs disclose and confirm their tobacco-free status. The disclosure entitles the index adolescent to participate in a lottery taking place just before the summer break.Interactive classroom education is conducted by trained school personnel in all classes during grades 6 (or 7) to 9. This education consists of age-specific information and practical exercises (eg, how to identify and resist social influences). For the purpose of this evaluation, the educational part was further structured and manualized before training personnel.

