	**Decline in school prevalence of never smokers**		
		Population	Students registered in the grades 7-9 of the schools participating in the experimental study and in the schools serving as external reference during three consecutive years
		Intervention 1	Tobacco-free Duo 6 components (as treated)
		Intervention 2	Educational component of Tobacco-free Duo only (as treated)
		Comparator	Usual education or health promotion
		Outcome	Average point prevalence of never smoking in spring term of each school year

^a^PICO: population, intervention, comparator, outcome.

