Participating students in schools randomized to Tobacco-free Duo or education only	Paper questionnaire, with information on: Cigarette and snus use (any, current, frequency, quitting) Tobacco use among friends and family members Received education, knowledge and attitudes toward tobacco Recent and current use of alcohol Ever use of illicit drugs General health, physical activity, and sedentary time Perceptions about the contract (if appropriate)	Self-administered in the classroom	Unique study code matched to identity information	Baseline: fall term of school year 1- grade 7 Follow-up 1: end of school year, grade 7 Follow-up 2: end of school year 2, grade 8 Follow-up 3: end of school year 3. grade 9
Guardians of the participating students above	Paper questionnaire, with information on: Sociodemographics Relation with the index child and perception of risks with tobacco use Own tobacco and alcohol use	Self-administered at home	Same code as the index child above	Same time points as above
Adults in Tobacco-free Duo pairs	Paper questionnaire, with information on: Own use of cigarette and snus Perception of own role in the intervention	Self-administered at home	Same code as the index child above	Anytime a contract is signed
All students registered in Tobacco-free Duo schools, education-only schools and reference group schools in grades 7-9	Paper questionnaire, with information on: Ever, regular and recent use of cigarette and snus	Self-administered in the classroom	No identifier (anonymous survey)	Cross-sectional surveys at the end of school year 1, 2 and 3

Figure 1 displays a scheme of the participants’ enrollment and assessments time-points for the experimental part of the study.

Individual data from questionnaires will be optically scanned, and the corresponding electronic files will be stored in a password-protected section of the server at the Department of Global Public Health, Karolinska Institutet. In order to preserve strict confidentiality, this data will be stored without personal identifiers, substituted by a study code unique to each participant. Personal identifiers will be kept in a separate section of the same server, only accessible to 2 members of the study team, responsible for data linkage and follow-up procedures, respectively. Ten years after the study start the personal identifiers will be removed and all information will be kept identified only through the study code.

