On the other side, participants in an experiment (be they organizations or individuals) constitute an imperfect representation of the underlying populations on which the inference should be drawn, because of the numerous selection steps involved in the conduction of an experiment [36]. In this study, we plan to include a comparison group that comprises schools that agreed to participate in annual surveys among all students in the 3 final compulsory grades but did not agree to be randomized to either experimental group. These schools are likely to well-represent the majority of Swedish schools (ie, the subgroup consisting of those that would not adopt the intervention if offered it at the scaling-up stage). By comparing the development over time of tobacco use in these schools with that of schools randomized to the minimal or comprehensive intervention (across a set of school-level characteristics), we aim to infer the added effect of the intervention on decline in tobacco uptake. For instance, if the prevalence of lifetime smoking or tobacco use similarly declines in reference group schools as in the randomized ones, we may project that the impact of a large and intensive dissemination of the intervention (even if effective in the randomized comparison) would be minimal.

Furthermore, we propose the use of qualitative methods and of process data in order to achieve 2 additional objectives. The first objective to be pursued is a deeper understanding of how the conduction of the intervention may differ between school organization characteristics. This knowledge is important in order to judge cluster-level confounding in nonrandomized studies [37]. An additional advantage of such a piece of knowledge would be the possibility to make projections of the potential benefits deriving from the application of the method to large communities with a known distribution of the studied characteristics.

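### Question 7 tracks a grades 7–9 average although the programme starts in grade 7, so a similar trend in the reference schools cannot support the Discussion's projection of minimal impact

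*Protocol article*

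**What the plan says.** Table 1, Objective 3, Question 7 asks about "total prevalence of never smokers among students in the grades 7 to 9 declining more slowly over 3 years" in Duo schools, compared with education-only schools or external reference schools. Table 2 fixes the outcome as "Average point prevalence of never smoking in spring term of each school year", over students in grades 7–9. Table 3 gives the timing: "Cross-sectional surveys at the end of school year 1, 2 and 3". These surveys are anonymous, and none precedes the intervention.

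Under Effectiveness Evaluation, "the start of the intervention was set in the seventh grade". The article does not say whether the new grade 7 classes of years 2 and 3 also receive the programme. The general description under Components says: "Interactive classroom education is conducted by trained school personnel in all classes during grades 6 (or 7) to 9".

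The reference group is "a convenience sample of schools in the same broad catchment areas where the experiment takes place", made up of schools that would join the surveys but not the experiment. The Results section reports 43 randomized and 16 reference schools. The Discussion then offers an example: "if the prevalence of lifetime smoking or tobacco use similarly declines in reference group schools as in the randomized ones", the authors may project that wide dissemination would have minimal impact, even where the randomized comparison shows the programme to be effective.

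**The concern.** A grades 7–9 average has the same age mix each spring. Smoking onset shows when a cohort ages from grade 7 to grade 9, and this average does not follow a cohort. Its trend is secular change plus whatever part of the programme effect reaches the average. With no survey before the intervention, an effect already present at the end of year 1 is subtracted from the trend.

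The expected direction is also unsettled. Question 7 presumes that never smoking falls. The Discussion's example has lifetime smoking falling, which means that never smoking rises. In that case a slower decline in never smoking has no meaning.

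At stake is the conclusion about dissemination. Similar trends in schools that were not randomized can come from self-selection (in either direction), from dilution or from low precision. None of these shows that the programme would do little. The Data Analysis section says that this comparison is meant to estimate potential impact on release, and the Introduction says that the evaluation was commissioned to inform possible recommendations.

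**Working it through.** **The plan's target.** Estimation of Sample Size gives control prevalence 0.70, risk ratio 1.10, ICC 0.02, cluster size 50, attrition 20%, 5% level and 80% power.

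- Intervention prevalence: 1.10 × 0.70 = 0.77, a 7-point difference in grade 9.
- Two-sided, no continuity correction: n per arm = [1.96√(2 × 0.735 × 0.265) + 0.842√(0.70 × 0.30 + 0.77 × 0.23)]² / 0.07² = 623.
- Design effect: 1 + 49 × 0.02 = 1.98. Then 623 × 2 × 1.98 = 2467, and 2467 / 0.80 = 3084, within 3% of the stated 3000.

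The 7 points are therefore the plan's own target, for Duo against education-only. The article gives no power for Question 7.

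**Dilution.** Assumptions: equal grade sizes, and one third of the effect gained per year of exposure (7/3 = 2.33 points). Whole-school difference in points:

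| Rollout | Year 1 | Year 2 | Year 3 | Change, year 1 to 3 |
|---|---|---|---|---|
| First grade 7 cohort only | 2.33/3 = 0.8 | 4.67/3 = 1.6 | 7/3 = 2.3 | 1.6 |
| Every new grade 7 cohort | 2.33/3 = 0.8 | (2.33 + 4.67)/3 = 2.3 | (2.33 + 4.67 + 7)/3 = 4.7 | 3.9 |

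If the first cohort alone gained the full 7 points within year 1, the difference would be 2.3 at every survey and the change would be 0.

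**Precision, Duo against reference, final prevalence.** SE = √{p(1 − p)[1 + (m − 1)ICC]/m × (1/k₁ + 1/k₂)}.

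- k₁ = 43/2 = 21.5 (equal split assumed) and k₂ = 16.
- m = 225 is assumed: 3000/40 = 75 per grade, times 3.
- ICC = 0.02 is the plan's value, assumed to hold for whole schools. Design effect: 1 + 224 × 0.02 = 5.48.
- p is assumed. With p = 0.75, SE = 2.23 points. With p = 0.773 (the mean over grades of 0.847, 0.773 and 0.70, from a straight line between 0.92 at baseline and 0.70 in grade 9), SE = 2.16 points.
- Power = Φ(difference/SE − 1.96). For 2.33 points it is 18–19%. For 4.67 points it is 55–58%.
- Over ICC 0.01–0.05 and 150–265 students per school (p = 0.773), power is 11–30% for the first cohort only and 30–82% for every new cohort.
- The 95% interval half-width is 1.96 × 2.16 = 4.2 to 1.96 × 2.23 = 4.4 points, about as large as the larger of the two effects.

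**Same contrast, change from survey 1 to survey 3.** SE = √{2p(1 − p)[(1 − ICC)/m + ICC(1 − c)] × (1/k₁ + 1/k₂)}, where c is the assumed cluster autocorrelation. With p = 0.773 and c = 0.5–0.8, power is 10–14% for the first cohort only and 38–59% for every new cohort.

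**Grade 9 alone, change from survey 1 to survey 3, Duo against education-only.** Same formula with m = 75, p = 0.735, k₁ = k₂ = 21.5 and a 7-point effect, taking grade 9 at survey 1 as unexposed. For c = 0, 0.5 and 0.8 the SE is 3.46, 2.89 and 2.49 points, and power is about 52%, 68% and 80%. Against the 16 reference schools it is about 46%, 61% and 74%.

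**The case against.** Objective 3 sets out to explore whole-school prevalence, so including less exposed grades is part of the question, and grade 9 by allocation is already Question 1. This stands in part: the average is a legitimate summary and should stay. It cannot carry an inference of minimal impact, however. The grade 9 survey comparison also does not merely repeat Question 1, because the anonymous surveys cover all registered students and the trial cohort covers those with consent.

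Detailed modelling may well sit in the analysis plan. The outcome and the wording of Question 7 are fixed in this article, though.

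The Data Analysis section also compares final prevalence, and the Discussion makes the comparison across school-level characteristics. Final prevalence keeps the year 1 effect, but it remains diluted and exposed to differences that existed before the programme. Neither provision supplies precision.

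Four stronger readings are tempting and are not supported:

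- A reader might infer that minimal impact is the likely conclusion even if the programme works as targeted. Rollout is not stated, a similar decline is nowhere defined as a non-significant test, and the 7 points are against education-only, so the effect against usual practice could be larger or smaller.
- A reader might infer that the reference comparison overrules the randomized result. The sentence is a hedged example in the Discussion, it concerns dissemination, and it leaves the randomized finding standing. Intention-to-treat analysis remains primary.
- A reader might infer that the two trial arms are pooled, because students "in both experimental groups will be contrasted to students in a convenience sample of schools". The text does not say so, and Table 2 lists the arms separately.
- A reader might infer that Table 2 treats the randomized contrast as an as-treated one. The comparator in that block is usual education.

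**Conclusion.** The concern holds for the estimand, the wording of Question 7 and the Discussion's inference. The grades 7–9 trend mixes secular change with a diluted effect and loses whatever is present by the end of year 1. Question 7 and the Discussion's example assume opposite directions.

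On the plan's own target the year 3 whole-school difference is about 2.3 to 4.7 points. Power against the reference schools on final prevalence is about 18–58% at ICC 0.02. These figures rest on linear build-up, equal grade sizes, 225 students per school, and the education-only target carried over to usual practice. They show that a similar trend is weak evidence of no impact. They do not give the probability of a wrong conclusion.

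That the projection is unsound does not depend on the exact figures, because self-selection alone could produce similar trends. The primary analysis is unaffected. The change is worth making because it governs what the study can say about dissemination.

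**What to change.** - Analyse the anonymous surveys by grade and year. Record grade if it is not already recorded; Table 3 does not list it.
- Compare the survey 1 to survey 3 change in grade 9 never smoking between Duo and education-only schools by allocation. Report Duo against reference schools as descriptive, with a confidence interval.
- Keep the grades 7–9 average as a summary.
- Reword Question 7 without a direction: whether the change in never-smoking prevalence differs between groups.
- State whether later grade 7 cohorts receive the programme, and whether grades 8 and 9 received any component in year 1. If they did, grade 9 at survey 1 is not an unexposed baseline.
- Replace the Discussion's minimal-impact example with a projection from the randomized estimate and its interval.

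The cost is mostly wording: the surveys are the same, with at most one added item for grade. The whole-school average becomes a descriptive summary, and the grade 9 change still has only about 52–80% power for 7 points.
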